### Trial population

The trial population will consist of adults (≥16 years old) presenting to NHS urology departments with a stone ≤25 mm in the lower pole of the kidney confirmed by non-contrast CTKUB. The patient and clinician must agree that active intervention is appropriate to remove the lower pole stone, and patients must be able to undergo either treatment for the specific stone size and be capable of giving informed consent which includes adherence with the requirement of the trial. Patients with multiple stones will be eligible provided all stones in the lower pole measure ≤25 mm in maximum dimension and, if there are stones of any size elsewhere in the urinary system, that the lower pole stone is the priority for treatment. A list of study sites is available on the study website (www.puretrial.org).

### Selection of participants

Clinicians will assess patients presenting with lower pole kidney stone. This will be aided by patient and clinician trial publicity material. A screening log documenting brief details of potentially eligible patients but without personal identifiers will be kept at each site to provide a summary of reasons for non-inclusion in the study to inform the Consolidated Standards of Reporting Trials diagram and assess generalisability of trial findings.

### Planned inclusion and exclusion criteria

#### Inclusion criteria

Adults ≥16 years of ageLower pole stone ≤25 mm in maximum dimension with the decision to treat that stonePresence of stone previously confirmed by CTKUBAble and willing to undergo either treatment for the specified stone sizeCapacity to give informed consent to participate in the trial, which includes adherence to trial requirements

#### Exclusion criteria

PregnancyPatients with a co-existing stone that takes precedence in deciding treatment modality (such as an obstructing ureteric stone or large upper pole stone)Patients with health or other factors that are absolute contraindications to an intervention that they may be allocatedPatients unable to understand or complete trial documentation

### Recruitment and trial procedures

#### Identifying participants

Patients with lower pole stones eligible for PUrE may be referred electively to urology departments having had a stone identified opportunistically by abdominal imaging or during investigation of urinary tract symptoms. Alternatively, they may present as an emergency with loin pain or infection. We will therefore inform clinical teams at each trial site of the target population backed up by trial publicity and trial summaries. At an appropriate point during their initial assessment, patients will be informed about the trial and given or sent information about the trial including a patient information leaflet with the contact details of the local research team. Patients will be given adequate time to consider participating in the study. They will have the opportunity to take study information away with them if desired, in which case the local research team will contact the patient after at least 24 h to determine their interest. If the patient is interested, the research team will confirm eligibility and discuss the individual’s possible participation with the clinical team. If both patient and clinical team agree regarding participation, arrangements will be made for consent to study, randomisation and clinical discussion and timing of allocated treatment. Wherever possible these processes will be arranged to take place together during one visit. Patients who decline, those who are ineligible or those for whom one of the possible allocated treatments is unsuitable will be recorded without identifiers on a screening log.

#### Informed consent

The patient information leaflet explains that the trial is investigating the effectiveness of active interventions for stones in the lower pole of the kidney. Patients will be informed that, depending on stone size, the trial will investigate whether the use of FURS will be superior to ESWL (stones ≤10 mm) or to PCNL (stones >10 mm and ≤25 mm). Signed informed consent forms will be obtained from the participants in all centres. Participants who cannot give informed consent (e.g. due to incapacity) will be not be eligible for participation. The participant’s permission will be sought to inform their general practitioner that they are taking part in this trial. We will also take optional consent for agreement to be approached for further studies on kidney stones, and for long-term follow-up through their local and central NHS clinical records after their active trial participation has finished.

#### Randomisation and allocation

Eligible and consenting participants, who have previously had a CTKUB to confirm the presence and size of stone, will be randomised dependent on the stone size using the telephone interactive voice response randomisation application or via the web-based application — both hosted by the fully registered UK Clinical Research Collaboration Clinical Trials Unit at the Centre for Healthcare Randomised Trials (CHaRT) Health Services Research Unit in Aberdeen, UK. Participants with a stone ≤10 mm will be entered into RCT1 and randomised to either FURS or ESWL. Participants with a stone >10 mm and ≤25 mm will be entered into RCT2 and randomised to either FURS or PCNL. Participants will then follow the standard care pathway for the allocated treatment. All the treatments allocated by randomisation in the study are used in routine clinical practice and in this pragmatic trial patients are expected to be treated using normal local clinical pathways and guidelines. The only trial-specific interventions apart from randomised treatment allocation will be participant completion of outcome questionnaires. Adherence to the allocated intervention will be monitored by the trial office team.

#### Blinding

There can be no blinding of participants, clinical staff or the central trial team to the allocated trial arm due to the differing nature of the interventions.

#### Follow-up procedures

Eligible patients who have given signed informed consent to participate in the study will be asked to complete the EQ-5D-5L, 12-item short-form survey (SF-12), pain score (by the Numeric Rating Scale (NRS)) and use of analgesic questions at baseline prior to randomisation. A baseline clinical case report form (CRF) will also be completed that will include stone size measured as the maximum dimension on a CTKUB. They will then be randomised to either one of the interventions dependent on the size of the lower pole stone and placed upon the appropriate waiting list. Waiting time duration for the trial interventions will be recorded and monitored. Participants will be asked to complete the pain score (NRS), EQ-5D-5L and use of analgesic questions at a number of fixed and variable time points during their trial participation. Fixed points will be baseline, just prior to initial intervention, weekly up to 12 weeks after initial intervention (FURS, PCNL and first ESWL session) and at 12 months post-randomisation. Variable points after 12 weeks will be just prior and 1 week after any additional intervention (including planned additional sessions of ESWL and removal of stent) and during any other hospital admissions related to treatment of their lower pole kidney stone (such as admissions for pain control or infection). At 12 weeks following the initial intervention, and at 12 months post-randomisation, participants will be asked to complete questions relating to their primary and secondary care use and their associated travel. At 12 months post-randomisation participants will be asked to additionally complete the SF-12. Participants will also be given the opportunity to complete an EQ-5D-5L at their discretion throughout the duration of the trial. A subset of 100 participants will receive the Cambridge Renal Stone Patient Reported Outcome Measure [34], a disease-specific health-related quality of life tool, at baseline, pre-intervention and at 12 weeks post-intervention.

Reminders may be used; for the earlier time points this may be a text message or email on the day that the questionnaire is due and, for the later time points (e.g. 12 weeks and 12 months), this reminder will be sent approximately 2 weeks and 4 weeks after the questionnaire is due.

We will offer and use all methods of delivery and collection of questionnaires and reminders including use of research teams for time points associated with hospitalisation, postal mail, email, web-based, telephone and SMS text, taking into account each participant’s stated preferred means of receiving and completing the measures. Participants will be sent a voucher (of modest value) as a token of appreciation for completion and return of the questionnaires.

CRFs collecting information on received care process and outcome will be completed by site research teams at baseline, following each initial and subsequent additional intervention (including planned additional ESWL sessions and stent removal), at 12 weeks post-intervention, after any additional stone-related treatments (e.g. admissions due to pain or infection) and 12 months post-randomisation. These will be entered at site into the web-based trial management platform.

To measure the secondary clinical outcome of stone clearance, participants will have kidney imaging at between 8 and 12 weeks according to clinical need and participant convenience. We will state preference for imaging by CTKUB during site initiation, but renal ultrasound and plain x-ray will be acceptable according to patient preference, safety and local practice. We will ask local site clinical teams (radiologist/urologist) to state whether there is: complete clearance of the target stone from the urinary tract defined as no further action or observation required for that stone; acceptable clearance where observation is required but no intervention planned; and unacceptable clearance where further intervention will be required. The maximum dimension of the largest remaining fragment in millimetres will also be recorded.

#### Withdrawal procedures

Participants are free to withdraw consent to participate at any time. Outcome data derived from medical records will be collected for those that withdraw unless the participant specifically withdraws their consent for this. All data collected up to the point of withdrawal will be retained and used in the analysis. Failure to undergo allocated treatment either because of participant preference or change of circumstance will not result in withdrawal and the participant will continue to participate in trial procedures unless consent to the trial is withdrawn.

### End of trial

The end of participation in the trial for each participant is defined as the final data capture to answer the research question: the 12-month post-randomisation questionnaire and CRF or the 12-week post-intervention questionnaire and CRF, whichever comes last.

### Safety

The PUrE trial involves procedures for treating lower pole stones that are all well established in current NHS clinical practice. Adverse effects may occur during or after any type of surgery. We will monitor serious adverse events and the local Principal Investigator or their delegate at the site will categorise these as expected or unexpected. Only serious unexpected adverse events related to the trial interventions or death of a participant will be notified to the Sponsor and Ethics Committee.

Hospital visits (planned or unplanned) associated with further interventions or complications of treatment (e.g. expected adverse events) due to the lower pole stone will be recorded as an outcome measure but will not be reported as serious adverse events. Other serious adverse events related to the intervention will not be reported a serious adverse event, but will be recorded in the CRFs. Planned primary care or hospital visits for conditions other than those associated with the lower pole stone will not be collected or reported. All deaths for any cause (related or otherwise) will be recorded on the serious adverse event form.

Within PUrE, ‘related’ is defined as an event that occurs as a result of a procedure required by the protocol, whether or not it is either the specific intervention allocated at randomisation or administered as an additional intervention as part of normal care.

### Provisions for post-trial care

Standard care is provided within the UK NHS.

### Outcome measures

#### Primary outcome measure

The primary outcome measures are health status measured by EQ-5D-5L AUC to 12 weeks post-intervention, based upon EQ-5D-5L completion at fixed time points (at baseline (recruitment), just prior to initial intervention (FURS, PCNL or first session of ESWL), weekly up to 12 weeks after initial intervention) and at variable time points (just prior to any additional intervention (including planned additional ESWL sessions and removal of stent) and once during hospitalisation for adverse events related to treatment (e.g. pain and infection)), and incremental cost per QALY gained at 12 months post-randomisation based on the estimated NHS costs and participant responses to the EQ-5D-5L (including an additional time point at 12 months).

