## Methods

### Trial objectives

The aim of this study is to determine which of FURS, PCNL and ESWL offers the best treatment outcomes in terms of clinical effectiveness and cost effectiveness for people with lower pole kidney stones seeking treatment within the UK NHS. An initial pilot phase will be built in to the trial to assess feasibility of recruitment and check appropriateness of eligibility criteria and outcome measures. The research question to be addressed is: in people requiring treatment for lower pole stones of the kidney does FURS with laser lithotripsy result in better quality of life than standard treatment with ESWL or PCNL according to stone size, and is it cost-effective for the UK NHS?

The clinical effectiveness and cost effectiveness of FURS as the first treatment option in comparison to ESWL for stones ≤10 mm in maximum dimension or PCNL for stones >10 mm and ≤25 mm in maximum dimension will be determined with respect to: 1) patient-reported health status measured as area under the curve (AUC) of the EuroQol five dimensions five-level version (EQ-5D-5L) questionnaire completed at multiple time points up to 12 weeks post-intervention; 2) incremental cost per quality-adjusted life year (QALY) at 12 months post-randomisation; 3) successful stone clearance at 12 weeks; 4) further interventions required to treat stones within 12 months of randomisation; and 5) treatment-related harms experienced up to 12 months after randomisation.

The null hypotheses being tested are: 1) the use of FURS to treat lower pole kidney stones ≤10 mm will not be different to ESWL as assessed by the EQ-5D-5L AUC up to 12 weeks post-treatment; 2) the use of FURS to treat lower pole stones of the kidney >10 mm and ≤25 mm will not be different to PCNL as assessed by the EQ-5D-5L AUC up to 12 weeks post-treatment.

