### Data collection and processing

#### Measuring outcomes

Outcome data will be collected throughout the trial for each participant from consent until 12 months following randomisation. See Table 1 for the schedule of events.

**Table 1 Tab1:** Source and timing of measures

		Timing					
		Intervention (PCNL or first session ESWL/FURS)					
		Weeks post intervention				Additional intervention (pre and post if >12 weeks) or treatment-related hospitalisation	Post- randomisation 12 months
Outcome measure	Source	Baseline^a^	Pre	1 to 11	12		
Health status EQ-5D-5L	PQ	✓	✓	✓	✓	✓	✓
Pain	PQ	✓	✓	✓	✓	✓	✓
Health profile SF12	PQ	✓	✓		✓		✓
Use of analgesics	PQ	✓	✓	✓	✓	✓	✓
Stone clearance (imaging)	CRF				✓^b^		✓
Additional interventions received	CRF&PQ				✓	✓	✓
Complications	CRF&PQ				✓	✓	✓
NHS primary and secondary healthcare use	CRF, PQ		✓		✓	✓	✓
Participant costs	PQ		✓		✓		✓

*CRF* case report form, *PQ* participant completed questionnaire

^a^Baseline is after informed consent has been given but prior to randomisation

^b^stone imaging performed at 8-12 weeks post treatment

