### Sample size, proposed recruitment rate and milestones

#### Sample size

The primary outcome is the AUC measured from multiple completions of the EQ-5D-5L by each participant up to 3 months following initial intervention (FURS, PCNL or first session of ESWL). In order to detect a standard deviation difference of 0.3, with 90% power, and alpha set at 5%, 235 participants per group (470 in total) are required. Such a difference in generic health status is considered clinically relevant and, in terms of treatment effect size, in the small to medium range as observed in other clinical studies. To allow for the anticipated 10% of participants for whom outcome data will be completely missing, and therefore the AUC cannot be calculated, it is proposed to randomise 522 participants in both RCT1 and RCT2, giving a total trial population of 1044 participants.

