### Statistical analysis

The primary outcome — health status AUC — will be generated for each participant using the trapezoidal rule. Data for participants who have missed a scheduled time point will be estimated using a multiple imputation approach to make use of partial outcome data. Sensitivity analyses will be conducted to assess the robustness of the treatment effect estimate to these approaches. The primary outcome measure will be analysed using linear regression with adjustment for design variables. Secondary outcomes will be analysed using generalised linear models with adjustment for design and baseline variables as appropriate. Subgroup analyses will explore the possible modification of treatment effect by important factors (centre, participant body mass index, stone size (maximum dimension and volume), stone density on CTKUB (Hounsfield units), skin to stone distance). We will also explore within each allocated group whether technical factors modify the treatment effect (access sheath versus no access sheath and digital versus non-digital instrument (FURS); fixed-site versus mobile device (ESWL); calibre of access track (PCNL)). This will be done by including treatment-by-factor interactions in the model and they will be classified as exploratory analyses. All analyses will initially be performed on an intention-to-treat basis, although we will consider additional analysis groups such as per-protocol if indicated. The main statistical analyses will be based on all participants as randomised, irrespective of subsequent compliance with the treatment allocation. All treatment effects sizes will be summarised by estimates and 95% CIs from the appropriate models. From the feasibility phase we will report estimates of recruitment rates and potential participant availability, together with appropriate CIs. There are no planned interim outcome analyses; all analyses will occur following completion of trial follow-up. Interim analyses will be performed if requested by the Data Monitoring Committee (DMC).

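### The primary EQ-5D-5L AUC lists the recruitment measurement as an input, so read literally its window is waiting time plus 12 weeks, with start and scaling not fixed

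*Protocol article*

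**What the plan says.** Under Primary outcome measure, the clinical primary outcome is "health status measured by EQ-5D-5L AUC to 12 weeks post-intervention". The section goes on to name the measurements that feed this area. It is "based upon EQ-5D-5L completion at fixed time points (at baseline (recruitment), just prior to initial intervention", and to these are added the weekly completions and some event-driven ones. The 12-month QALY comes later in the same sentence, with its own extra time point.

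The footnote to Table 1 places the recruitment measurement in time: "Baseline is after informed consent has been given but prior to randomisation". After randomisation, participants join the list for their allocated procedure. On the wait, Follow-up procedures says only: "Waiting time duration for the trial interventions will be recorded and monitored". End of trial lets participation run to the 12-month questionnaire or "the 12-week post-intervention questionnaire and CRF, whichever comes last".

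Under Statistical analysis, the AUC "will be generated for each participant using the trapezoidal rule". The primary model is a linear regression adjusted for design variables. Adjustment for baseline variables is mentioned for the secondary outcomes, but not for the primary one.

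Elsewhere only the end of the window is given. The null hypotheses speak of a difference "as assessed by the EQ-5D-5L AUC up to 12 weeks post-treatment", and the Sample size section says "The primary outcome is the AUC measured from multiple completions of the EQ-5D-5L by each participant up to 3 months following initial intervention".

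**The concern.** Suppose the listed time points are taken at their word and joined by the trapezoidal rule. The curve then begins at recruitment and ends 12 weeks after treatment. Its length is the participant's wait plus 12 weeks, and the wait happens after randomisation. Nothing in the protocol bounds it. The end-of-trial rule matters only if 12 weeks after treatment can fall later than 12 months after randomisation, so waits beyond about 52 - 12 = 40 weeks were foreseen as possible.

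Two things are at stake. If the AUC is an undivided total, time on the list is credited as health: spread in waits becomes noise, and any difference in mean wait between arms enters the treatment estimate in favour of the arm that waited longer. If the AUC is divided by its duration, untreated weeks are averaged in with treated ones and the treatment effect is diluted. The research question concerns health status after treatment, and neither version measures that cleanly.

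**Working it through.** **Inputs from the protocol.** Target 0.3 SD, 90% power, 5% alpha, 235 per group, 10% with no outcome data, 522 per RCT (Sample size); AUC time points (Primary outcome measure); trapezoidal rule (Statistical analysis).

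**Inputs that are assumptions.** The documents give no utilities, SDs or waits. I take a mean utility u of 0.7 to 0.9, a between-person SD s of mean utility of 0.10 to 0.25, and various waits W in weeks.

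**1. The plan's own figure.** For a two-sided test the normal approximation gives 234 per group and the t-test version 234.5, so 235. Power at 235 per group is 90%. Then 470/0.9 = 522.2 (stated 522) and 2 x 522 = 1044. The stated numbers reproduce.

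**2. The window as written.** Let E0 be utility at recruitment, E1 utility just before treatment and A the area over the 12 weeks after treatment. The trapezoidal rule gives

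total AUC = W x (E0 + E1)/2 + A.

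The first term grows with W whatever the treatment does.

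**3. Undivided total, unequal mean waits.** Each extra week adds about u, that is 0.7 to 0.9 utility-weeks. A 0.3 SD effect on the 12-week area is 0.3 x s x 12. The difference in mean wait that produces the same amount is (0.3 x s x 12)/u:

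| s | Target, utility-weeks | Weeks at u = 0.7 | Weeks at u = 0.8 | Weeks at u = 0.9 |
|---|---|---|---|---|
| 0.10 | 0.36 | 0.51 | 0.45 | 0.40 |
| 0.15 | 0.54 | 0.77 | 0.68 | 0.60 |
| 0.20 | 0.72 | 1.03 | 0.90 | 0.80 |
| 0.25 | 0.90 | 1.29 | 1.12 | 1.00 |

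So about 0.4 to 1.3 weeks would match the whole target.

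**4. Undivided total, equal mean waits.** Treat a participant's utility U as constant and independent of W, with W having mean m and SD w. The variance of U x (W + 12) is

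(s² + u²)(w² + (m + 12)²) - u²(m + 12)².

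With s = 0.20, u = 0.8, m = 8, w = 4: 0.68 x 416 - 0.64 x 400 = 26.88, so the SD is 5.18, against 12 x 0.20 = 2.40 for the 12-week area. A true effect of 0.72 utility-weeks is then 0.72/5.18 = 0.139 SD, and power at 235 per group is about 33%. Over s = 0.15 to 0.25 (u = 0.8) and waits of mean (SD) 8 (4), 12 (6) and 12 (8) weeks, power runs from 12% to 37%.

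This holds the target at 0.3 of the 12-week SD. If 0.3 SD is instead read against the wider SD, power stays at 90%, but the effect needed becomes 0.3 x 5.18 = 1.55 utility-weeks. That is 1.55/12 = 0.13 in mean utility over the 12 weeks, instead of 0.72/12 = 0.06.

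**5. AUC divided by its duration.** The gain from waiting as such disappears. An effect present only after treatment is multiplied by 12/(12 + W): 75% at 4 weeks, 60% at 8, 50% at 12, 32% at 26. If the SD of the average stays at s, 60% turns 0.3 SD into 0.18 SD, with power about 50%. If waiting-period utility is only partly correlated with later utility, the SD of the average falls and the loss is smaller.

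**6. Fixed window from treatment to week 12.** W drops out, and 235 per group gives 90% power as planned.

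**The case against.** The strongest reply is that no sentence says the window opens at recruitment. The objectives and the Sample size section give only the end. The description of ESWL uses the first session as the reference point for timing outcome assessments, which suits a clock that starts at treatment. The list of completions could be a schedule shared with the QALY, which does need a baseline. This has some force: the start is a literal inference, not a stated definition. It does not remove the point, because the list is attached to the AUC and the QALY follows with its own addition.

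A second reply is that scaling is a matter for the analysis plan. That is fair for scaling alone. It does not cover the inclusion of recruitment among the AUC points, which the article itself states.

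Stronger readings are tempting, and the documents do not support them.

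- A reader might infer that the plan does favour the arm that waits longer. That needs an undivided AUC and unequal mean waits, and neither is stated. Outpatient ESWL and theatre-based FURS might plausibly have different lists, but that argument reaches RCT1 only. In RCT2 both procedures are operations, and the two RCTs are analysed separately.
- A reader might infer that the trial is underpowered. The arithmetic reproduces, the target is set in SD units of the AUC, and the power figures in steps 4 and 5 rest wholly on assumed inputs.

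It is also fair to say that a treatment-anchored window is not free: it starts after randomisation and leaves never-treated participants without an AUC. The protocol keeps such participants in the trial and analyses everyone as randomised, so any fix has to deal with them.

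**Conclusion.** The concern holds in a conditional form. The protocol makes the recruitment EQ-5D-5L an input to the primary AUC, ends the AUC 12 weeks after treatment, and states neither scaling nor adjustment for waiting time or baseline EQ-5D-5L. Read literally, this integrates over an uncapped, participant-specific wait plus 12 weeks. This is a badly fixed outcome definition, not an error of calculation.

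Both ways of scaling cause harm, but of different kinds: noise and possible bias for a raw total, dilution for a time-averaged one. The sizes shown depend on assumed utilities, SDs and waits and should be read as illustrations. Whether bias arises at all depends on whether mean waits differ between arms, on which the documents are silent. Because the definition serves the clinical primary outcome of both RCTs, it should be settled before either is analysed.

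**What to change.** State the primary AUC as follows, in the protocol and the analysis plan:

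- The window is a fixed 12 weeks, with the pre-intervention EQ-5D-5L as time zero, then the weekly points to week 12, on a fixed 12-week scale.
- The recruitment EQ-5D-5L enters the model as a covariate only, not as part of the area.
- Participants who never receive an intervention enter the as-randomised analysis by a stated rule, for example a reference date fixed in advance or imputation, with a sensitivity analysis.
- Waiting time and waiting-period utility are reported by arm in each RCT.

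This uses data already scheduled and leaves 235 per group and 522 per RCT unchanged. The cost is a choice of estimand: the window opens at an event after randomisation, and health during the wait leaves the clinical primary outcome. It stays in the 12-month QALY counted from randomisation. The by-arm report of waits lets readers judge how far the post-randomisation start matters.
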